# ‘Fit Moms/*Mamás Activas*’ internet-based weight control program with group support to reduce postpartum weight retention in low-income women: study protocol for a randomized controlled trial

**DOI:** 10.1186/s13063-015-0573-9

**Published:** 2015-02-25

**Keywords:** Postpartum, WIC, Internet-based, Lifestyle intervention, Weight retention, Pregnancy

## Abstract

**Background:**

High postpartum weight retention is a strong independent risk factor for lifetime obesity, cardiovascular disease, and type 2 diabetes in women. Interventions to promote postpartum weight loss have met with some success but have been limited by high attrition. Internet-based treatment has the potential to overcome this barrier and reduce postpartum weight retention, but no study has evaluated the effects of an internet-based program to prevent high postpartum weight retention in women.

**Methods/Design:**

Fit Moms/*Mamás Activas* targets recruitment of 12 Women, Infants and Children (WIC) Supplemental Nutrition Program clinics with a total of 408 adult (>18 years), postpartum (<1 year) women with 14.5 kg or more weight retention or a body mass index of 25.0 kg/m^2^ or higher. Clinics are matched on size and randomly assigned within county to either a 12-month standard WIC intervention or to a 12-month WIC enhanced plus internet-based weight loss intervention. The intervention includes: monthly face-to-face group sessions; access to a website with weekly lessons, a web diary, instructional videos, and computer-tailored feedback; four weekly text messages; and brief reinforcement from WIC counselors. Participants are assessed at baseline, six months, and 12 months. The primary outcome is weight loss over six and 12 months; secondary outcomes include diet and physical activity behaviors, and psychosocial measures.

**Discussion:**

Fit Moms/*Mamás Activas* is the first study to empirically examine the effects of an internet-based treatment program, coupled with monthly group contact at the WIC program, designed to prevent sustained postpartum weight retention in low-income women at high risk for weight gain, obesity, and related comorbidities.

**Trial registration:**

This trial was registered with Clinicaltrials.gov (identifier: NCT01408147) on 29 July 2011.

## Background

Of the approximately four million women who give birth in the United States each year, an estimated 25% experience major weight gain after pregnancy, retaining more than 4.5 kg [1,2]. High postpartum weight retention is particularly prevalent (40 to 60%) in low income Hispanic women [3-9] and women facing food insecurity [10-13]. High postpartum weight retention is a strong independent risk factor for several long-term health consequences for the mother, including a continued trajectory of weight gain over time [14,15] and increased risk of lifetime obesity, cardiovascular disease, and type 2 diabetes. Moreover, women with high postpartum weight retention are heavier prior to their next pregnancy, which increases the risk of pregnancy-related complications, obesity, and obesity and serious health complications in the offspring [16-21]. Overweight and obese women are at high risk of postpartum weight retention and face compounded risks associated with obesity and high postpartum weight retention [22].

### Challenges in reducing postpartum weight retention

Efforts to promote postpartum weight loss in high weight retainers have met with some success and yielded short-term weight losses of 4.8 to 7.8 kg [23-26]. Lovelady *et al.* [23] promoted weight loss in newly postpartum (four weeks) overweight women with a 10-week eating and exercise program; results indicated that intervention participants lost 4.8 kg, while control participants lost 0.8 kg. Similarly, O’Toole *et al.* [25] found that a structured diet and exercise program that included weekly and bi-monthly group meetings promoted significant changes in weight and body fat relative to a self-directed control group at one-year postpartum. Leermakers *et al.* [24] designed a weekly correspondence-based behavioral intervention delivered for six months during the postpartum year in women who had retained more than 6.8 kg of their pre-pregnancy weight. Women in the correspondence group lost 7.8 kg compared to only 4.9 kg in the no-treatment control group. These weight losses compare favorably to those seen in postpartum weight loss and other behavioral programs that include weekly treatment meetings [27].

However, while effective in promoting weight loss, existing postpartum interventions have had several limitations. Interventions have been short-term (≤6 months) and generally experienced high attrition (30 to 40%). During the postpartum period, women are busy with childcare and multiple new demands, making attendance at weekly face-to-face interventions problematic [22]. Moreover, existing interventions have paid little attention to the cultural, social, and contextual factors that influence postpartum body weight [22]. Lack of a theoretical framework may underlie this shortcoming [28]. Finally, existing programs have generally failed to target a population at greatest risk for postpartum weight retention, including low-income, multiethnic women.

Lifestyle interventions during pregnancy can prevent excessive gestational weight gain and reduce postpartum weight retention in many women through six months postpartum [29-37]. However, despite intervention, the majority (50 to 70%) of women - and low-income women in particular - continue to experience high postpartum weight retention, and, by 12 months postpartum, there are no significant differences between intervention and control groups [29,30,38]. Although there are benefits to intervening during pregnancy, effective postpartum interventions are still needed to sustain positive changes instituted during pregnancy and to help women with high postpartum weight retention when pregnancy interventions appear ineffective.

### Internet-based treatment holds promise in reducing postpartum weight retention

Over the past decade, internet use has increased exponentially in the United States and most rapidly among young adult, low-income, and minority sub-groups [39-44]. In the United States, an estimated two out of three adults and 75% of adults under the age of 50 use the internet, with 88% of users having access from home [40-42,45]. Similar usage rates are prevalent among low-income women [46]. The flexibility of an internet-based weight control program could accommodate postpartum women who face many unpredictable time and childcare demands that have limited their attendance at traditional face-to-face treatment programs.

The internet has been shown to be effective in promoting significant weight loss in obese non-postpartum patient populations [47-50]. Randomized controlled trials have shown that programs delivered via the internet are effective in a variety of patient populations when they mimic standard face-to-face interventions (participants receive weekly lesson material); they submit weekly diaries and individualized email feedback is sent to the participant [47-50]. These programs have produced weight losses of 6 to 8 kg at three and six months and 4 to 8 kg at 12 [50] and 18 [47] months in non-postpartum populations. Participant retention in these programs is higher than standard face-to-face interventions, with retention rates of 80 to 84% at one year [47,50]. Less intensive internet-based weight loss programs available to the general public (for example, interactive dieting websites) that do not provide personalized feedback have had very limited effects [51,52]. However, the effectiveness and flexibility of comprehensive online behavioral treatment are potentially ideal for postpartum women who face many unpredictable time and childcare demands yet report high motivation for weight control [53-57].

### Reaching underserved postpartum women

The government-funded Women, Infants and Children (WIC) Supplemental Nutrition Program is designed to improve the nutritional status and health of low-income, nutritionally-at-risk pregnant or lactating women and children under five-years-old by providing supplementary food (in the form of coupons or checks redeemable for specific food items), nutrition education, and referrals. WIC has been in place for over four decades and serves eight million low-income women and their families each month nationwide [58]. Almost half of pregnant women in the United States and/or their children enroll in WIC at some point during their postpartum year [59]. California has the second largest WIC program in the nation, serving about 1.4 million participants monthly [60]. Evaluation research has documented improved nutritional outcomes from WIC participation, but no formal weight loss program is in place [61-65]. WIC commonly uses the internet to provide nutrition education to its patients, and patients report a preference for using the internet due to its ease and format [66]. In one of the few evaluations of a WIC website, a study of 39,541 self-selected women in the WIC program found that 75% had access to the internet from home [46]. Use of the website (was associated with significant improvements in readiness to change on a variety of domains, including picky eating, breastfeeding, and physical activity [46,66,67]. However, an internet-based intervention to reduce postpartum weight retention has neither been formally provided nor tested as part of the WIC program, where an estimated 40 to 60% of women experience high postpartum weight retention [11-13].

### Social cognitive theory

Social cognitive theory (SCT) emphasizes the dynamic interplay of the individual and the environment in adopting long-term behavior change. SCT suggests that a ‘resilient’ sense of self-efficacy must be developed to perform weight control behaviors (being physically active and eating a low-calorie diet) and needs to be developed over time through a series of mastery experiences. Those mastery experiences must promote changes in the use of self-regulation skills (planning, self-monitoring, problem solving, self-standards, goals, and self-incentives) to foster weight control and healthy eating and exercise behaviors. SCT further suggests the process of behavior change and maintenance is enhanced through social support and an awareness of the individual’s ecology. Weight control intervention does not rely solely on individual-level information, external reinforcement, or self-regulation, but it embeds a more dynamic approach to self-regulation (adaptive self-regulation skills) within the network of social influences germane to an individual’s ecology. Intrapersonal, interpersonal, and organizational and institutional supports are garnered to address particular barriers to change (such as limited time for physical activity or meal preparation, and unsafe neighborhoods) and practice changes within specific cultural contexts [68,69]. SCT thus provided a rich basis for promoting weight loss in low-income, multiethnic, postpartum women, capitalizing on the internet’s cost efficiencies, tailoring ability, ready and long-term access, and reach [70].

### Study aims

Fit Moms/*Mamás Activas* is a cluster randomized clinical trial funded by the National Institute of Diabetes, Digestive, and Kidney Diseases (NIDDK). The clinical site is at California Polytechnic State University, San Luis Obispo ([name], Principal Investigator (PI)) and an additional performance site that is overseeing development and delivery of the online and text-messaging intervention is the University of North Carolina at Chapel Hill ([name], PI). In this cluster randomized trial, 12 WIC clinics are randomized to receive the standard WIC program for 12 months or the enhanced WIC plus internet-based postpartum weight loss program. The primary hypothesis is that the enhanced WIC plus internet postpartum weight loss program will produce significantly greater weight losses than the standard WIC at six and 12 months.

Secondary aims will determine whether the enhanced WIC plus internet postpartum weight loss program will result in greater improvements in eating and exercise behaviors (examined at 0, six, and 12 months) and psychosocial parameters (depression, social support, self-efficacy, body image, and stress) than standard care. The study will examine the proportion of women who achieve pre-pregnancy weight at six and 12 months and identify baseline characteristics that may moderate the efficacy of the intervention (such as ethnicity, socioeconomic status, pre-pregnancy weight, parity, and breastfeeding status). The study will also examine the relationship between changes in behaviors, psychosocial factors, and weight changes during the 12-month period. These evaluations will help identify the mechanisms by which the intervention produces greater success compared to the standard WIC.

## Methods/Design

### Study design

As noted, Fit Moms/*Mamás Activas* is a cluster randomized (with fractional cross-over) trial evaluating the long-term effects of a comprehensive internet-based behavioral weight loss intervention for postpartum women. Twelve WIC clinics (with 408 postpartum women with excessive weight retention) are randomized within three counties to either a 12-month standard WIC intervention or to a 12-month WIC enhanced plus internet-based weight loss intervention (Figure 1). Assessments are conducted at baseline, six, and 12 months. Although the intervention’s primary target is the individual, and most of the intervention will occur outside of the clinic setting, we selected a randomized cluster design to reduce the likelihood of within-clinic contamination through patient interactions with other patients, or with WIC clinicians who are reinforcing use of the internet intervention. This study was approved by the Cal Poly Human Subjects Committee (approval number: 000001118; internet-based intervention and registered at Clinicaltrials.gov (identifier: NCT01408147). All participants in the study will provide informed, written consent using the Institutional Review Board-approved consent form.

**Figure 1 Fig1:**
[figure not shown]
**Fit Moms/**
***Mamás Activas***
**cluster randomized design.**

### Clinic and participant recruitment

A total of 12 clinics (six in Santa Barbara county, four in San Luis Obispo county, and two in Ventura county) were selected for inclusion in this study. The clinics were selected because they are representative of California state WIC populations, are willing to accept randomization, and agreed to the study’s recruitment and intervention protocols. At these clinics, a combined total of 408 participants (34 per clinic) are targeted for recruitment. Blinded study research assistants are screening woman attending their postpartum visits, using our pre-established screener [71,72]. Women who appear interested in the program are asked to complete a permission to be contacted card and are then screened by phone; phone screening is done (rather than on-site screening) to ensure patient privacy and limit potential burden on WIC clinics of requiring private screening rooms during recruitment. If still eligible after screening, patients will be asked to attend an orientation meeting, complete informed consent, and are scheduled for baseline screening visits. Once sample sizes are met at a given clinic, recruitment is closed at the clinic. The flow chart of these stages of recruitment is shown in Figure 2.

**Figure 2 Fig2:**
[figure not shown]
**Overview of Fit Moms/**
***Mamás Activas***
**.**

### Eligibility criteria

Table 1 describes the eligibility and exclusion criteria for this trial. These criteria were selected to identify a representative postpartum population at greatest risk for weight gain and obesity-related co-morbidities. As indicated, women must be between six weeks and 12 months postpartum. Similar to other studies [24], we selected this period to strike a balance between allowing enough time for initial pregnancy-related weight loss to occur, while still intervening early enough to prevent long-term postpartum weight retention, which has been independently related to future weight gain and the development of obesity [15]. Women must be currently overweight or obese, with a body mass index (BMI) of 25 kg/m^2^or more or have a BMI between 22 and 24.9 and exceed pre-pregnancy weight by at least 4.5 kg (10 lb) [73]. On average, by six weeks postpartum, women retain 3 to 6.8 kg of the weight gained during pregnancy, with Hispanic populations falling into the higher end of this range [6,8]. A greater than 6.8 kg weight retention after six weeks postpartum would represent a significantly higher than average weight retention [6,8], increasing the risk of major weight gain later in life.

**Table 1 Tab1:** **Inclusion and exclusion criteria for Fit Moms/**
***Mamás Activas***

**Inclusion criteria**	
	Between six weeks and 12 months postpartum
	BMI ≥25 kg/m^2^ or have a BMI between 22 and 24.9 25 kg/m^2^ and exceed pre-pregnancy weight by at least 4.5 kg (10 lb).
	18 to 40 years
	English- or Spanish-speaking
	Non-smoking
	Primiparous or multiparous
	Lactating or non-lactating
	Literacy ≥5^th^ grade level
	Cell phone
**Exclusion criteria**	
	Pregnancy or planning pregnancy
	Relocating in the next year
	Serious current physical disease (such as heart disease, cancer, renal disease, or diabetes) for which physician supervision of diet and exercise prescription is needed
	Physical problems that limit the ability to exercise
	History of eating disorders
	Current problems with drug abuse
	Current treatment for a serious psychological disorder

As indicated, women must be also be between 18 and 40-years-old; English- or Spanish-speaking; non-smoking; primiparous or multiparous; lactating or non-lactating [23,74-76]; and have adequate literacy (at a fifth grade level or beyond). Participants who do not have a computer and/or internet access from home are provided with a laptop computer and/or internet access for study use. Those with limited computer experience will receive training until they demonstrate proficiency in accessing online materials. As internet access is increasing exponentially in this country, we wanted this study’s findings to be relevant to most all populations, as internet access will likely reach the vast majority of the American population in years to come [44]. Cell phone access at time of study entry is also required. Any type of cell phone is acceptable (the phone does not have to have a smartphone). Participants whose computers or cell phones break are loaned a replacement on a temporary basis.

Exclusion criteria (Table 1) were developed to maximize the safety of the intervention and minimize attrition. These include pregnancy, planning pregnancy, relocating in the next year, serious current physical disease (such as heart disease, cancer, renal disease, or diabetes) for which physician supervision of diet and exercise prescription is needed, physical problems that limit the ability to exercise [77], a history of eating disorders [78], current problems with drug abuse, or current treatment for a serious psychological disorder (such as schizophrenia or bipolar disorder). Up to 10% of postpartum women may experience depression [79]. Women with significant depressive symptoms (Beck Depression Inventory score >20 [80-82]) require provider approval (for example, from a social worker or physician) prior to enrollment or are referred for appropriate care.

### Randomization and masking

Randomization is computer-generated by the statistician. Specifically, randomization is conducted at the clinic level, stratified by county, and designed to ensure balance in treatment arms. Four clinics were crossed-over (in random order) in order to allow for estimation of some within-clinic effects. We decided to stratify randomization by county to control for any chance imbalance due to potentially unmeasured regional or administrative differences. We decided against further stratifying based on ethnicity and pre-pregnancy BMI due to the small likelihood of a chance imbalance, given the demographic similarity of the clinics, and limited evidence that these variables impact treatment response among postpartum (or other) women [83,84]. Within each randomized clinic, participants are sequentially selected until target sample sizes are met (please see Sample size calculation section**).**

Recruiters and assessors are blinded to the clinic randomization, and participants are not told their assigned treatment status until after enrollment. Several procedures are in place to ensure blinding among clinic recruiters, assessors, and potential enrollees. In brochures and the study consent form, the study is presented identically at both control and intervention clinics. There is a minimal amount of cross-over activity between clinics, but the study’s branded items are distributed at both intervention and control clinics as part of retention so that the study logo is a familiar sight. The recruiters and assessors have little to no contact with individuals aware of treatment assignment, including the WIC county chiefs and intervention research assistants.

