### Institutional and interpersonal level intervention

#### Brief clinic visits

WIC public health aides and dietitians spend five minutes during patients’ regularly scheduled WIC visits (typically every three months) to reinforce use of the internet-based program. After WIC practitioners logon to the WIC check-in system, they receive an alert and instructions to provide the patient with a specific Fit Moms/*Mamás Activas* color-coded card, tailored to each patient’s level of adherence to logging on to the website and attending groups. The WIC counselors review the cards and encourage patients to use the Fit Moms/*Mamás Activas* site and to attend groups. We considered allocating a greater role for the WIC practitioners at these visits (such as discussing weight loss progress, goal setting, problem solving, and motivation interviewing). However, the scripted message and simplicity of the protocol were praised by the WIC staff during our design phase and have been designed to fit into the busy WIC practice setting, provide institutional-level support for the intervention, and enable delivery by both public health aides and dietitians. More extensive professional support is provided by study interventionists at monthly groups.

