#### Sample size calculation

The targeted sample size (12 clinics; 34 participants per clinic; total N = 408) is projected to provide ≥80% power to detect a meaningful difference in weight change at 12 months as small as 2 kg between group means, when the standard deviation is 4.5 kg and the intraclass correlation (ICC) is 0.02, using a two-sided *t*-test with a significance level of 0.05, and accommodating anticipated rates of loss to follow-up (30% participant attrition at 12 months). Although we do not anticipate clinic attrition, 10 clinics (five in each condition) would provide 80% power to detect a difference in weight change as small as 2 kg. An ICC of 0.002 was estimated from results of our pilot demonstration trial and a WIC survey study [130], but we have conservatively used an ICC of 0.02 for sample size calculations [131]. For secondary aims, in our most conservative estimates [25], we would have greater than 80% power to detect both medium and large effects (Cohen’s d = 0.5 and 0.8, respectively) for any continuous or categorical outcome variable at the alpha = 0.05 level using a two-sided test of significance.

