#### Analysis plan

The primary outcome measure, change in weight from baseline over time, is assessed at six and 12 months. All measured weights will be included in the analyses. The analysis strategy is based on a conceptual framework that explicitly recognizes that both differences between individuals within clinics and between clinics may contribute to variance in weight change. Randomly assigned group (standard care versus intervention) is the main independent variable for intention-to-treat (ITT) analyses. County is a stratification variable for randomization and is expected to be balanced across intervention and standard care groups by design. Our analysis approach uses linear mixed-effect models to analyze differences between the intervention and standard care clinics allowing for within-cluster variation (participants within the same clinic) and within-individual variation (repeated measures) [132]. The model will include factors for a fixed effect for treatment and group and random effects for clinic as well as a group × time interaction term to test if the change over time in the dependent variable differs significantly for the two study groups. In addition, for primary and secondary outcomes, the model will include participant-level covariates to adjust for any baseline differences, or adjust for covariates that may relate to the outcome, including lactation, age, age at menarche, education, income, smoking status, language, socioeconomic status, race and ethnicity, height, pre-pregnancy BMI, parity, gestational gain, inter-pregnancy interval, baseline BMI, and changes in marital status and employment [2,133-139] In addition, the model will include terms to account for whole-clinic (cluster-level) variants, including Latina proportion, lactation proportion, mean age, mean education, and mean SES.

Our study design will give rise to temporally repeated measurements, and some subjects may be lost to follow up. In the primary analysis, missing weight measurements will be assumed missing at random, but diagnostic analyses will be conducted related to missing data (for example, comparing baseline characteristics of completers versus non-completers and creating propensity scores). If missing data appear to have the potential of influencing interpretation, we will also conduct multiple imputations using several different models for non-ignorable missingness. These will be used to assess the range of impact that missing data may exert on our results.

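### Four of the 12 clinics deliver both arms in sequence, yet the primary model has no period or clinic-by-period term and no analysis addresses possible carry-over

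*Protocol article*

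**What the plan says.** The Study design section calls this a "cluster randomized (with fractional cross-over) trial". It gives the reason for randomising clinics: "we selected a randomized cluster design to reduce the likelihood of within-clinic contamination through patient interactions with other patients". The same sentence goes on to name clinic staff as a further source: "or with WIC clinicians who are reinforcing use of the internet intervention". Two routes of contamination are thus named, peers and clinic staff.

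Randomization and masking then adds: "Four clinics were crossed-over (in random order) in order to allow for estimation of some within-clinic effects". The article does not give the split of orders, the number of women per period or any gap between periods.

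Brief clinic visits describes the staff route in the intervention arm ("The WIC counselors review the cards and encourage patients to use the"); what the counsellors promote is the study website and group attendance.

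The Analysis plan specifies the primary model: "The model will include factors for a fixed effect for treatment and group and random effects for clinic". A group-by-time interaction is there to "test if the change over time in the dependent variable differs significantly for the two study groups". Time here is the participant's own follow-up (baseline, six and 12 months), not the clinic's recruitment period. About 17 participant covariates and five clinic case-mix terms follow. Period, sequence and carry-over are not among them, and no analysis is given of the within-clinic effects for which the clinics were crossed over.

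The Sample size calculation section does not mention the cross-over. Its fallback, "10 clinics (five in each condition) would provide 80% power", is that of a parallel design.

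**The concern.** In one third of the clinics both arms run in the same place, one after the other. Two consequences follow for the estimate.

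First, within a crossed-over clinic the treatment contrast is a before/after contrast. If more clinics start with intervention than with control, or the reverse, any calendar change in weight loss falls partly on the treatment effect. The Cluster-level assessment section plans to record programme, policy and environmental changes each year, so the investigators regard such change as possible. The model has no term that would absorb it.

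Second, in a clinic that goes from intervention to control, later controls meet staff who have been reinforcing the programme and perhaps women who have taken part in it. These are the two routes that clustering was meant to limit. Any carry-over would pull the estimate toward zero.

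The model is otherwise set out term by term, so this is a mismatch between the stated design and the stated model and not only a detail left for later.

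**Working it through.** **Inputs from the article.** 12 clinics of 34 women; 30% attrition; SD 4.5 kg; ICC 0.02; difference 2 kg; two-sided 5% level; four crossed-over clinics.

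**Assumptions, because the article is silent.** 17 women per period in each crossed clinic (keeps the total at 408); eight parallel clinics, four per arm; correlation between two periods of one clinic 0.8 times that within a period; order 2:2 unless stated.

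**1. The plan's own figure.** Completers per clinic: 34 × 0.7 = 23.8. Design effect: 1 + 22.8 × 0.02 = 1.456. Effective n per arm: 6 × 23.8 / 1.456 = 98.1. SE = 4.5 × √(2/98.1) = 0.643 kg. Power for 2 kg is 87.5% (normal) or 80.1% (t, 10 df). For five clinics per arm, effective n is 81.7 and power is 81.1% (normal) or 70.2% (t, 8 df). So the stated power reproduces as a purely parallel calculation. Whether the 10-clinic figure holds depends on the choice of degrees of freedom, which is separate from the cross-over.

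**2. The layout described.**
- Between-clinic variance: 0.02 × 20.25 = 0.405. Within-clinic variance: 19.845.
- Crossed clinics, 11.9 completers per period. Variance of the mean within-clinic difference: 2 × (0.405 × 0.2 + 19.845/11.9) / 4 = 0.874.
- Parallel clinics recruiting over both periods. Variance of the difference: (2/4) × (0.405 × 0.9 + 19.845/23.8) = 0.599.
- Weight on the crossed clinics: (1/0.874) / (1/0.874 + 1/0.599) = 0.407.
- SE: 1/√(1/0.874 + 1/0.599) = 0.596 kg. Power 91.8% (normal) or 85.5% (t, 10 df).
- If the parallel clinics recruit only in the first period, their variance is 0.619, the weight 0.415 and the SE 0.602.

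**3. Calendar shift of 1 kg, no period term.** The mean within-clinic difference moves by 0 kg at 2:2, 0.5 kg at 3:1 and 1 kg at 4:0. Multiplying by the weight gives a bias of 0, about 0.20 and about 0.41 kg (0.21 and 0.41 with weight 0.415). The sign depends on which order is in excess and on the direction of the shift. A period term removes the bias. It leaves the SE unchanged at 2:2; the SE becomes 0.607 to 0.624 at 3:1 and 0.641 to 0.710 at 4:0, the higher values applying if parallel clinics recruit in one period only.

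**4. Carry-over at 2:2.** Controls after intervention number 2 × 17 = 34 of 204, or 16.7%. If they receive a fraction f of the 2 kg, half of the crossed clinics have their difference cut by 2f, so the mean within-clinic difference falls by f kg and the estimate by 0.407 × f.
- f = 0.25: 2 − 0.10 = 1.90 kg
- f = 0.50: 2 − 0.20 = 1.80 kg (1.79 with weight 0.415)
- f = 1.00: 2 − 0.41 = 1.59 kg

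A simple head count (16.7% × f × 2 kg) would give 1.92 and 1.83 kg for the first two; the mixed model gives the crossed clinics more weight than their share of women. Adding a period term does not change any of these estimates at 2:2. If each crossed clinic instead recruited 34 per period, the first two become 1.86 and 1.72 kg, but the total would then exceed 408.

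**5. Leaving out clinic-by-period variance.** A model with only a random clinic effect reports an SE of 0.596. If parallel clinics recruit in one period, the true SE is 0.602 at a correlation ratio of 0.8 and 0.626 at 0, so the reported SE is about 1% to 5% too small. If they recruit in both periods, the understatement is below 1%.

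**6. Omitting control periods that follow intervention.** At 2:2 with a period term, the SE is 0.643 kg if the parallel clinics recruit in both periods and 0.691 kg if in one. Power is 87.5% or 82.5% (normal), and the estimate is free of the carry-over modelled here.

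**The case against.** The strongest reply has four parts.

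**Contamination is not shown.** This stands. Website access is by personal login, groups are closed to newcomers and led by study staff, and the counsellors' cards depend on the patient's own logins and attendance, which controls do not have. Most of the intervention takes place outside the clinic. A reader might infer that controls are contaminated and the effect is diluted; the article supports only that this could happen, in controls enrolled after an intervention period. The 25% to 50% range is an assumption.

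**Period terms belong in the analysis plan.** This stands only in part. A separate plan may exist and the article does not say that its list is exhaustive. But it specifies the model closely, down to clinic-level case-mix, and gives a purpose for the cross-over that no listed analysis serves.

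**Order was random and the parallel clinics anchor the comparison.** True, and at 2:2 a calendar shift causes no bias. But random order does not guarantee 2:2 among four clinics, and the split is not reported.

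**No power is lost.** This stands. A reader might infer that power stated for a parallel design must be too high for this one. Without carry-over the mixed layout has more power than the parallel calculation (91.8% against 87.5%, normal). At 25% carry-over it is still 88.9% (normal) or 81.8% (t); at 50%, 85.4% or 77.5%.

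**Conclusion.** The point holds as a mismatch between design and model. Four clinics run both arms in sequence, which sits against the stated reason for clustering, and the primary model and the listed analyses make no allowance for period or carry-over.

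The size is modest and conditional: a bias of about 0.2 kg (3:1) or 0.4 kg (4:0) for an assumed 1 kg calendar shift, and a true 2 kg estimated as about 1.90 to 1.79 kg at an assumed 25% to 50% carry-over with a 2:2 order. Both rest on 17 women per period and on a between-period correlation that the article does not give.

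Two stronger conclusions are not supported. The missing period term is not what would cause dilution: that would come from exposure of controls, and the term alone does not remove it. And no shortfall in power follows from ignoring the cross-over in the sample size.

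**What to change.** - Add a fixed period effect and a clinic-by-period random effect to the primary model. Define period by the clinic's recruitment phase, distinct from follow-up time.
- Pre-specify a sensitivity analysis that omits control periods following an intervention period in the same clinic. This is needed because the period term alone does not deal with carry-over.
- State, for the four crossed-over clinics, the order, the number of women per period and any gap between periods.
- Describe the sample size for eight parallel and four crossed-over clinics, without implying that the stated power for 12 clinics was too high.

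The cost is wording and one extra analysis; no more participants are needed. The period term costs no precision at 2:2 and a little if the orders are unequal (SE 0.596 to 0.607 at 3:1 with recruitment in both periods). The clinic-by-period variance will be weakly estimated with only four crossed clinics, so the plan should say what is done if it is estimated at zero or the model does not converge.
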